# Efficacy of pancreatic enzyme replacement therapy (PERT) in the treatment of gastrointestinal symptoms after gastric cancer surgery: study protocol for a multicenter randomized controlled open-label trial

**DOI:** 10.3389/fphar.2026.1779727

**Published:** 2026-03-11

**Keywords:** gastric cancer, gastrointestinal symptoms, pancreatic enzyme replacement therapy, pancreatic exocrine insufficiency, surgery

## Abstract

**Introduction:**

Pancreatic exocrine insufficiency (PEI), presenting as bloating or diarrhea, affects 26%–100% of patients after gastrectomy, delaying recovery and impairing quality of life. Pancreatic enzyme replacement therapy (PERT) is the standard PEI management, yet its efficacy after gastric cancer surgery remains controversial. This study evaluates PERT’s effectiveness in alleviating postoperative gastrointestinal symptoms.

**Methods and Analysis:**

In this multicenter randomized controlled trial, 204 patients undergoing radical gastrectomy will be randomized 1:1 to PERT or control. The PERT group will receive Pancreatin Enteric-coated Capsules (containing 450 mg pancrelipase microgranules) three times daily with meals for 1 month post-discharge. The primary outcome is the incidence of gastrointestinal symptoms at 1 month post-surgery, assessed using the MD Anderson Symptom Inventory Gastrointestinal Cancer Module (MDASI-GI). Secondary outcomes include nutritional status and treatment compliance.

**Discussion:**

This protocol establishes a framework for definitively evaluating PERT in gastric cancer patients. Results will inform evidence-based PEI management, with significant implications for survivorship care. By integrating patient-reported outcomes and nutritional metrics, we aim to validate a patient-centered strategy optimizing functional recovery after curative resection.

**Clinical Trial Registration:**

This study was registered with the Chinese Clinical Trial Registry (ChiCTR; registry number: ChiCTR2500102557). Date of registration: 16 May 2025.

## Introduction

1

Gastric cancer ranks as the fifth leading cancer for both mortality and morbidity worldwide (Sundar et al., 2025). In 2022, approximately 360,000 patients were diagnosed with gastric cancer and 260,000 died from the disease in China (Zheng et al., 2024). Gastrectomy and D2 lymphadenectomy still play a crucial role in the treatment of gastric cancer. However, more than half of the patients suffered from gastrointestinal symptoms after surgery (Xu et al., 2022), such as abdominal distention, pain, diarrhea, which delayed patient recovery and affected quality of life.

Certain postoperative gastrointestinal symptoms are caused by pancreatic exocrine insufficiency (PEI). Clinical symptoms of PEI include steatorrhea, weight loss, bloating and malnutrition (Whitcomb et al., 2023). PEI is characterized by deficient enzyme secretion, leading to maldigestion, malabsorption, and malnutrition (Ghodeif, 2023; Whitcomb et al., 2023). Some studies showed that the incidence of PEI following gastrectomy was 26%–100% (St et al., 2017; Heneghan et al., 2015), which may be related to the absence of neural gastric reflexes, bacterial overgrowth, extensive denervation of the pancreas and asynchrony between delivery of the pancreatic enzymes and the food particles (Iivonen et al., 1998; MacGregor et al., 1977; Domínguez-Muñoz, 2009; Leth et al., 1991). Oral pancreatic enzyme replacement therapy (PERT) is the mainstay of treatment for PEI. Few studies have addressed PERT following gastrectomy for gastric cancer. Some studies founded that patients with gastrectomy got the symptomatic benefit of PERT, a positive response was seen in 78.9% (71.9%–85.2%) (Guman et al., 2022; Moore et al., 2023; Veeralakshmanan et al., 2020). However, another study considered that PERT had no effect on steatorrhea, bowel movements and observation time were only 14 days (Brägelmann et al., 1999). To date, there is no consensus on the use of pancreatic enzyme replacement therapy for gastric cancer after surgery and whether pancreatic enzyme replacement therapy can alleviate postoperative gastrointestinal symptoms is still unclear.

In this multicenter randomized controlled trial, we aim to evaluate efficacy of pancreatic enzyme replacement therapy (PERT) in the treatment of gastrointestinal symptoms after gastric cancer surgery.

## Methods and methods

2

### Trial design

2.1

The PERT-GC01 trial is a multicenter randomized controlled trial (ChiCTR Identifier: ChiCTR2500102557), gastric cancer following radical gastrectomy will be randomized in a 1:1 ratio to the PERT group or the control group. A randomization schedule will be generated by computer to assign subjects to the treatment sequences. A total of 204 patients will be recruited from seven large-scale gastrointestinal medical centers in China which include Sichuan Cancer Hospital, Chengdu First People’s Hospital, Chengdu Second People’s Hospital, Chengdu Third People’s Hospital, Mianyang People’s Hospital, Mianyang Third People’s Hospital and Langzhong People’s Hospital. This study was approved by the Ethics Committee for Medical Research and New Medical Technology of Sichuan Cancer Hospital (SCCHEC-02-2025-008). The study design is summarized in Figure 1.

**FIGURE 1 F1:**
[figure not shown]
Flowchart of the study.

### Eligibility criteria

2.2

The inclusion and exclusion criteria for patients were listed in Table 1.

**TABLE 1 T1:** The inclusion and exclusion criteria for this study.

Inclusion criteria	
1	Male or female aged 18–75 years.
2	Histologically confirmed gastric adenocarcinoma and feasible radical resection for gastric cancer.
3	Eastern Cooperative Oncology Group (ECOG) score of 0 or 1.
4	The main organ function is normal.
5	Informed consent form signed.
Exclusion criteria	
1	Other active malignant tumors within 5 years or at the same time.
2	History of pancreatic disease within half a year.
3	Distant metastasis confirmed by imaging or pathological examination.
4	Allergic to any component of the therapy.
5	Human immunodeficiency virus (HIV) infection.
6	Vulnerable groups, including mentally ill, cognitively impaired, critically ill patients, minors, pregnant or lactating women, illiterate, etc.
7	Severe postoperative complications, including anastomotic fistula, intestinal obstruction, abdominal bleeding, severe infection.
8	Stop taking the experimental medication for more than 2 weeks.

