### Interventions

2.3

After discharge, all enrolled patients will be advised to consume their diet as tolerated, with a focus on eating 5–6 meals per day to avoid gastrointestinal overload. Moreover, patients in PERT group will oral Pancreatin Enteric-coated Capsules (produce by Abbott laboratories GmbH, H20171150), each capsule contains 150 mg pancrelipase microgranules (lipase 10,000 U. Ph. Eur., amylase 8,000 U. Ph. Eur., protease 600 U. Ph. Eur.) which was derived from pig pancreas. The Capsules are commercially available and issued by the project team. According to guidelines (Dominguez-Muñoz et al., 2025; Smith et al., 2016; Gheorghe et al., 2015), we design that the patients after discharge take three capsules (30,000 U) with food three times a day for 1 month in this study. The first participant was enrolled on 6 June 2025.

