### Follow-up

2.5

The MDASI-GI and NRS2002 were assessed by patients via Wenjuanxing App. Assessment of MDASI-GI, NRS2002, and blood samples for lymphocyte count, hemoglobin, serum albumin, and prealbumin were collected at baseline before surgery. Follow-up begins postoperatively and continues for 1 month after discharge. Assessment of MDASI-GI occurs at postoperative day 2 (POD 2), postoperative day 7 (POD 7), and twice weekly following discharge. NRS2002 and blood samples are collected once every 2 weeks after discharge (Figure 2). Patients’ self-reported Medication adherence will be recorded. If a patient decides to withdraw, the follow-up will be stopped.

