However, PEI is often ignored by medical staff, due to its the nonspecific nature of the symptoms and the absence of a simple diagnostic test (Croagh et al., 2023). Patient-Reported Outcome (PRO) report can easily make up for this deficiency, which is an important tool to assess the patient’s physical health, functional status, and posttreatment feeling without interpretation bias from the medical personnel (Fiore et al., 2018). We use the MDASI-GI to prioritize symptom burden from the patient perspective, which can better evaluate the effectiveness of PERT.

Furthermore, the PERT-GC01 study protocol enrolls gastric cancer patients who have undergone curative resection, irrespective of prior neoadjuvant therapy. This inclusive design aligns with contemporary clinical practice, where neoadjuvant treatment has become the standard of care. One-month follow-up is short, and will miss long-term outcomes, so further study still be needed.

This protocol establishes a framework for definitively evaluating PERT in gastric cancer patients. Results will inform evidence-based PEI management, with significant implications for survivorship care. By integrating patient-reported outcomes and nutritional metrics, we aim to validate a patient-centered strategy optimizing functional recovery after curative resection.

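### Exclusion criterion 7 (severe postoperative complications) has no time window and randomisation has no fixed day, so patients already allocated open-label can be excluded

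*Protocol article*

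**What the plan says.** All references are to the protocol article.

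- **Criterion 7.** Section 2.2, Table 1 excludes "Severe postoperative complications, including anastomotic fistula, intestinal obstruction, abdominal bleeding, severe infection". No period is attached.
- **Criterion 8.** The next row of Table 1 excludes patients who interrupt the study drug for longer than two weeks.
- **Point of randomisation.** The abstract has "204 patients undergoing radical gastrectomy will be randomized 1:1 to PERT or control". Section 2.1 has "gastric cancer following radical gastrectomy will be randomized in a 1:1 ratio to the PERT group or the control group". Neither names a day or an event such as discharge.
- **Entry.** Inclusion criterion 2 is worded as it would be before an operation: "Histologically confirmed gastric adenocarcinoma and feasible radical resection for gastric cancer". The Discussion says the trial "enrolls gastric cancer patients who have undergone curative resection".
- **Assessments and treatment.** Section 2.5 says baseline measures "were collected at baseline before surgery" and schedules symptom assessments on postoperative days 2 and 7. Under section 2.3, "the patients after discharge take three capsules (30,000 U) with food three times a day for 1 month".
- **Blinding.** The title reads "study protocol for a multicenter randomized controlled open-label trial".

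**The concern.** A severe postoperative complication can be recognised only in the days or weeks after surgery. If allocation takes place soon after the operation, some patients will meet criterion 7 with their arm already assigned. Even if allocation waits until discharge, the criterion has no end, so an obstruction or severe infection during the treatment month also fits its wording.

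Two things are at stake. The first is comparability. In an open-label trial, the staff who decide whether a complication is severe enough to exclude can know the arm. The primary outcome in section 2.4 counts pain, nausea, vomiting and abdominal distension among its seven symptoms, and obstruction or infection can plausibly produce these. Excluding such patients unevenly would remove likely events from one arm. The second is precision, because any such losses may come on top of the 10% dropout allowed for in section 2.6.

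**Working it through.** **Step 1: when can criterion 7 act?** Set the time points in order.

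| Time | What the article places there |
|---|---|
| Before surgery | Baseline measures; the wording of inclusion criterion 2 |
| After surgery, day unspecified | Randomisation (2.1) |
| Postoperative days 2 and 7 | Symptom assessments |
| After discharge | Study drug for 1 month |
| Any time after surgery | Criterion 7 as worded |
| After drug has started | Criterion 8 |

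Section 2.1 is compatible with any day from surgery to discharge. Criterion 7 is certain to precede allocation only if allocation is at discharge and the criterion stops there. The text states neither condition. Criterion 8 shows that Table 1 includes at least one rule that operates after allocation.

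**Step 2: do the analysis rules close the gap?** Section 2.7 defines the full analysis set by at least one dose and one evaluable efficacy outcome, and removes patients with adherence below 50%. It does not say that patients meeting criterion 7 after allocation are kept. A patient allocated to PERT early, who has a complication and never starts the drug, would leave the set under the one-dose rule.

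**Step 3: the planned sample size.** Inputs from section 2.6: 50% v 30%, two-sided 5%, 80% power, 10% dropout.

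Unpooled formula: n = (1.960 + 0.842)² × (0.5×0.5 + 0.3×0.7) / 0.20² = 7.849 × 0.46 / 0.04 = 90.3, so 91 per arm. Then 91 / 0.9 = 101.1, so 102 per arm and 204 in total. The stated figure reproduces. (The pooled-variance version gives 93, then 104 per arm, 208 in total.)

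**Step 4: power if more patients are lost (assumption).** The article gives no complication rate, so a range is shown. Let e be the share lost under criterion 7 beyond the 10% dropout. Then n = 102 × 0.9 × (1 − e) per arm, and power = Φ[(0.20√n − 1.960√0.48) / √0.46], where 0.48 = 2 × 0.4 × 0.6 is the pooled variance term and 0.46 the unpooled one.

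| e | n per arm | Power |
|---|---|---|
| 0% | 91.8 | 79.5% |
| 5% | 87.2 | 77.4% |
| 10% | 82.6 | 75.1% |
| 15% | 78.0 | 72.7% |

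For e = 10%: (0.20 × 9.090 − 1.960 × 0.693) / 0.678 = 0.678, and Φ(0.678) = 0.751.

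**Step 5: bias in the worst case (assumption).** Suppose there is no true effect (50% in both arms), 92 analysable patients per arm, and removal in the PERT arm only. If a share e is removed and a proportion s of those have symptoms, the apparent PERT rate is (0.5 − e·s) / (1 − e).

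| e | s | Apparent PERT rate | Spurious benefit | Chance of a false finding for PERT |
|---|---|---|---|---|
| 5% | 70% | 48.9% | 1.1 points | 3.4% |
| 10% | 90% | 45.6% | 4.4 points | 8.5% |
| 15% | 100% | 41.2% | 8.8 points | 20.8% |

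The nominal chance is 2.5% in that direction. If removal is equal in both arms, or comes before randomisation, this bias does not arise.

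**The case against.** The case for the plan is substantial.

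- **The wording on timing barely conflicts.** Section 2.1 and the Discussion both place the patients after resection. The abstract's phrase describes the population loosely, and a pre-operative baseline fits screening before surgery with allocation afterwards. This stands: a reader might infer that the article contradicts itself on when patients are randomised, but the text supports only a missing anchor with mildly varying wording.
- **Criterion 7 may be a screen before allocation.** With drug starting after discharge, that is a natural reading, and on it nobody is lost after randomisation. Figure 1 is not available here and may show the point. This also stands as a possibility. A reader might infer that allocated patients are being removed; no sentence says so. The screen reading is not secured either, because the criterion has no end and the next row of the same table acts after allocation.
- **Section 2.7 does not list complications as a reason to leave the analysis.** True. A patient who starts the drug, has a later obstruction and stays adherent would meet the stated conditions of the full analysis set. That leaves the analysis section and an open-ended exclusion criterion pointing in different directions, which needs settling.
- **Neither arm takes study drug before discharge**, so treatment cannot change complication rates in that window. Bias there would need unequal application of the criterion. This stands, and it makes the one-arm figures in step 5 a limit rather than an expectation.
- **The 5–15% range is assumed**, and section 2.6 does not say whether its 10% already covers such losses. Both are correct. The power figures are illustrations only.

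**Conclusion.** The point holds as a gap in the wording. Criterion 7 has no time window and randomisation has no stated day, so in an open-label trial the text permits exclusion of allocated patients, including some who are likely to have primary-outcome events. The documents do not show that this is done, nor that it differs by arm.

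The size is unknown. If 10% were lost beyond the 10% dropout, power would fall from about 79.5% to about 75%. The spurious benefit of 1.1 to 8.8 points applies only if 5–15% were removed from the PERT arm alone and 70–100% of them had symptoms. The sample size of 204 is not in question.

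The change is worth making: it is specific, it closes a route to bias, and it costs very little. Confidence is medium because Figure 1 may already fix the time point.

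**What to change.** 1. State one point of randomisation in the abstract, section 2.1 and Table 1: at discharge, after criterion 7 has been checked.
2. Limit criterion 7 to complications arising between surgery and randomisation.
3. State in section 2.7 that every randomised patient is analysed in the assigned arm for the primary outcome. This includes patients with a complication after randomisation and those already randomised; enrolment opened on 6 June 2025. Bring criterion 8 and the one-dose and adherence rules into line with that statement for the primary analysis.

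These changes concern who is randomised and who is analysed. How a complication is managed clinically is outside this point.

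The cost is a short amendment. If allocation is currently done earlier, it would be released a few days later, and the assessments on postoperative days 2 and 7, where they precede discharge, would become pre-randomisation measurements. The drug already starts after discharge, so treatment logistics stay the same. The number randomised stays at 204.

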### Outcomes

2.4

The primary outcome of the trial is the incidence of gastrointestinal symptoms at 1 month postoperatively in gastric cancer patients. Seven gastrointestinal symptoms (pain, dysphagia, nausea, vomiting, abdominal distension, constipation and diarrhea) are assessed using the MD Anderson Symptom Inventory Gastrointestinal Cancer Module (MDASI-GI) (Wang et al., 2010). We use a 0–10 numerical rating scale (NRS) to assess the severity of symptoms, with 0 being “not present” and 10 being “as bad as you can imagine.” Secondary outcomes include nutritional status and patient compliance. Nutritional status was assessed using the Nutritional Risk Screening 2002 (NRS 2002), Patients were classified as high risk when NRS score was 3 and low risk when NRS score was <3. In addition, hematological markers including lymphocyte count, hemoglobin, serum albumin, and prealbumin also reflected nutritional status, the lower the value, the more severity of malnutrition. Medication adherence in the PERT group is documented through Medication Record Cards.

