### Statistical analysis

2.7

Continuous variables will be presented as mean ± standard deviation (SD), and categorical variables will be presented as numbers (percentages). The χ^2^ or Fisher’s exact test apply to present the difference of the primary outcome. The t-test is used to demonstrate the statistical difference of the continuous variables such as MDASI-GI score, NRS2002 score and hematological indicators. In addition, the logistic regression (age, sex, nutrition status, style of gastrectomy, PERT will be included as influencing factors) will be used to identify the risk factors affecting the incidence of gastrointestinal symptoms. All randomly assigned patients who receive at least one dose of the study medication will be included in the full analysis set (FAS) according to the intention-to-treat (ITT) principle, and at least one evaluable efficacy outcome is used for the analysis of all efficacy outcomes and baseline characteristics of patients. Patients with study drug adherence of <50% will not be included in the analysis. Statistical significance was defined as a p-value less than 0.05.

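### Exclusion 8 in Table 1 (stopping study drug for more than 2 weeks) can be met only after randomisation and only in the PERT arm, so it is not an eligibility criterion and cuts against the claimed ITT analysis

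*Protocol article*

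**What the plan says.** The title describes a "study protocol for a multicenter randomized controlled open-label trial". Under Trial design (2.1), patients with "gastric cancer following radical gastrectomy will be randomized in a 1:1 ratio to the PERT group or the control group". Under Interventions (2.3), both arms receive dietary advice after discharge. Only one arm receives capsules: "Moreover, patients in PERT group will oral Pancreatin Enteric-coated Capsules", taken "with food three times a day for 1 month in this study". No control drug or placebo is described.

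Three rules bear on patients who stop the capsules:

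- **Table 1 (2.2), exclusion 8:** "Stop taking the experimental medication for more than 2 weeks". It stands in the same list as baseline criteria such as HIV infection and distant metastasis.
- **Follow-up (2.5):** "If a patient decides to withdraw, the follow-up will be stopped".
- **Statistical analysis (2.7):** "Patients with study drug adherence of <50% will not be included in the analysis". The same paragraph says that the full analysis set follows the intention-to-treat principle.

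Adherence is recorded in one arm only (Outcomes, 2.4): "Medication adherence in the PERT group is documented through Medication Record Cards".

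**The concern.** An eligibility criterion should be decidable before randomisation and should apply to both arms alike. Exclusion 8 does neither. If sites apply it, patients leave the PERT arm because of something that happened on treatment, and no matching patients leave the control arm. The arms are then no longer the groups that randomisation formed. If those who stop differ in symptom burden from those who continue, the comparison of symptom incidence is biased.

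Section 2.5 adds a second uncertainty. It ends follow-up at withdrawal without saying whether giving up the capsules counts as withdrawal. A site that reads exclusion 8 and section 2.5 together could reasonably end the app questionnaires for a stopper. An analysis plan could later reverse an exclusion from the analysis, but it could not restore scores that were never collected.

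**Working it through.** **Step 1: who can meet exclusion 8, and when.** Randomisation follows gastrectomy (2.1). Drug starts after discharge, in PERT only (2.3). A stop of more than 14 days therefore cannot exist at entry, and a control patient has no drug to stop.

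**Step 2: overlap with the adherence rule in 2.7.** For a course of D days with d days missed and full intake otherwise, adherence = (D − d)/D.

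| D | d = 15 | d = 16 |
|---|---|---|
| 28 | 13/28 = 46.4% | 12/28 = 42.9% |
| 30 | 15/30 = 50.0% | 14/30 = 46.7% |
| 31 | 16/31 = 51.6% | 15/31 = 48.4% |

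Nearly everyone caught by exclusion 8 is also below 50%. The exception is a stop of exactly 15 days in a 30- or 31-day course with almost perfect intake otherwise. The mismatch is wider the other way. A patient who takes one of the three daily doses throughout has adherence of 1/3, about 33%, and never stops. Section 2.7 drops that patient; Table 1 does not.

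**Step 3: the plan's own figure.** Section 2.6 gives 50% versus 30%, two-sided 5%, 80% power and 10% dropout. With unpooled variance:

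n = (1.96 + 0.842)² × (0.25 + 0.21)/0.20² = 90.3, so 91 per arm; 91/0.90 = 101.1, so 102 per arm and 204 in total.

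This matches the stated 204, so the sample size is not in question.

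**Step 4: size of the possible bias.** From the document: control incidence 50% and 102 per arm. Assumed, because the document gives neither: the share s of PERT removed, and the symptom incidence q among those removed. With no true effect, the PERT rate in those who remain is

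r = (0.50 − s × q)/(1 − s).

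For example, (0.50 − 0.10 × 0.80)/0.90 = 46.7% and (0.50 − 0.20 × 0.80)/0.80 = 42.5%.

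The rejection rate is the exact two-sided rate of the uncorrected χ² test at 5%, comparing 102 controls with 92 (s = 10%) or 82 (s = 20%) remaining PERT patients.

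| q among stoppers | PERT rate, s = 10% | Rejection | PERT rate, s = 20% | Rejection |
|---|---|---|---|---|
| 100% | 44.4% | 12.3% | 37.5% | 39.6% |
| 80% | 46.7% | 7.7% | 42.5% | 17.3% |
| 60% | 48.9% | 5.5% | 47.5% | 6.3% |
| 50% | 50.0% | about 5% | 50.0% | about 5% |
| 20% | 53.3% | 7.7% | 57.5% | 17.3% |

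The last row mirrors the 80% row, with the bias now against PERT. Starting instead from 92 per arm (102 less 10% dropout), the 80% row gives 7.3% and 16.2%, so the choice of n matters little.

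**The case against.** The strongest objection is that harm beyond the misplaced criterion is not shown. It has four parts.

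- **Data loss.** A reader might infer that a PERT patient who quits the capsules stops giving the primary outcome, so that the data would never exist. The document does not support this. Section 2.5 ties the end of follow-up to a patient's decision to withdraw and does not call stopping the drug a withdrawal. The adherence rule in 2.7 suggests the opposite, because dropping low adherers from an analysis presupposes that they are still in the data. This part stands: loss is possible, not stated.
- **Timing.** The primary outcome is at 1 month after surgery, while drug runs for 1 month after discharge. If discharge is around day 8 (an assumption), postoperative day 30 is about day 22 on drug. Only a stop beginning in roughly the first week (22 − 14 = 8) would then trigger exclusion 8 before that time point. This limits how many primary outcomes could go uncollected. It does not help once a patient is excluded, because Table 1 removes the patient whether or not the score exists.
- **Conflict with 2.7.** A reader might call the 15-of-30-day case a contradiction between Table 1 and 2.7. It is a knife-edge, as step 2 shows, and should not carry weight. Because the rules largely coincide, most of the bias in step 4 is shared with the <50% rule and is not additional to it. This stands too. But correcting 2.7 alone would leave exclusion 8 in force.
- **Direction.** Patients may stop because they feel unwell or because they feel well. The document does not say which, so a spurious benefit for PERT is only one scenario.

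The objection does not touch the core. Exclusion 8 is a rule that the article states, not a detail left to a fuller document, and it can act on one arm only.

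**Conclusion.** The point holds as a defect of design wording with a one-sided effect. A post-randomisation event that only PERT patients can have is listed as an eligibility exclusion, which is inconsistent with the ITT principle in 2.7. The article also leaves unclear whether those patients are still followed.

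Under no true effect, the consequence ranges from none (stoppers as symptomatic as everyone else) to type I error of about 8% to 17% (10% to 20% removed, 80% of them symptomatic), and it reverses in direction if stoppers have fewer symptoms. Those inputs are assumptions throughout. Confidence is moderate to high on the defect and low on the size and direction of the bias.

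**What to change.** - **Table 1:** remove exclusion 8 from the eligibility criteria and record the event as treatment discontinuation, with its date and reason.
- **Section 2.5:** state that patients who stop study drug continue the scheduled MDASI-GI, NRS2002 and blood assessments to the end of follow-up, and that data collection ends only if consent to follow-up is withdrawn.
- **Section 2.7:** analyse all randomised patients in the arm to which they were assigned, and keep adherence-based exclusions for a per-protocol sensitivity analysis.
- **Consistency:** reconcile 2.2, 2.5 and 2.7 so that one definition of stopping and one definition of low adherence apply throughout.

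These changes concern data collection and analysis only and alter no treatment rule. The cost is amendment wording and continued app prompts and blood samples for stoppers, using assessments already scheduled. The planned 204 is unchanged. Enrolment began on 6 June 2025, so any outcomes already missed cannot be recovered. The report should give the number of patients removed under exclusion 8 before the amendment.
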